**Inclusion Criteria**

1. Age greater than or equal to 21
2. Ambulance transport to WFBMC ED
3. Non-traumatic chest discomfort or other symptoms consistent with possible ACS
4. Patient being transported to WFBMC ED for further care

### Exclusion Criteria

1. ST-segment elevation in contiguous leads on any electrocardiogram (>/= 1 mV)
2. Inter-facility transfers
3. Short Pre-hospital times: Scene time + Transportation time anticipated to be less than 5 minutes.
4. Unstable vital signs: symptomatic hypotension at the time of enrollment (systolic < 90 mm Hg), tachycardia (HR>120), bradycardia (HR<40), and hypoxemia (<90% pulse-oximetry on room air or normal home oxygen flow rate)
5. Patient receiving hospice care
6. Concomitant non-cardiac medical, surgical, or psychiatric emergency

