**Participation**

The target population is adult patients with acute chest pain or other symptoms suggestive of ACS, but without obvious ACS on ECG, who are being transported to WFBMC ED. Therefore, patients >21 years old with acute chest pain, without evidence of an ST-segment elevation myocardial infarction (STEMI) on ECG, will be included. Based on STEMI rates at WFBMC we expect less than 5% of patients with acute chest pain to be excluded due to ECG criteria.

This pilot has been selected for implementation based on collaborations across multiple disciplines including Emergency Medicine, Cardiology, and Prehospital Medicine. As a quality improvement project with broad-based support from local and state EMS systems, participation by human subjects will be part of customary care. Patients treated and transported for acute chest pain by paramedics in Forsyth, Surry, and Stokes County, specifically trained for this investigation, will have data abstracted from their EMS records. In EMS quality assurance projects, it is customary for EMS agencies to contact their patients by phone to assess their well-being. Therefore, each patient will be contacted 30-90 days following their pre-hospital encounter to determine if they have had MACE (cardiac death, acute myocardial infarction, and coronary revascularization), hospitalizations, and objective cardiac testing (stress testing and coronary angiography). Patients will also have index and outcome data abstracted from their WFBH EMR. These data will be reviewed to ensure the feasibility and accuracy of pre-hospital chest pain risk stratification by paramedics using the HEART score and i-STAT POC troponin assay. These quality assurance activities will be performed under a waiver of informed consent, obtained from the Institutional Review Board, as is currently utilized for similar quality surveillance programs at WFBH (i.e. the HEART Pathway Implementation).

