
Next, we will begin implementation in ambulances in Forsyth County, Surry County, and Stokes County. Eligible patients for this observational pilot implementation will be adult patients, over 21 years old, with non-traumatic chest pain or symptoms concerning for ACS, being transported to WFBMC ED. Patients with acute ST elevation myocardial infarction on initial pre-hospital ECG and patients being transferred from another hospital will be excluded. In addition, patients will be excluded when paramedics estimate that the patient’s pre-hospital time (scene time + transportation time) will be less than 5 minutes.

Paramedics will use a worksheet to obtain the historical and clinical data needed to calculate a HEART score. This will include performing POC troponin testing. This is within the scope of practice of paramedics who routinely start IVs and perform POC testing on acutely ill patients. Furthermore, the feasibility of performing POC troponin analyses in a moving ambulance has been previously established.[^20-22^](#_ENREF_20) While the paramedics will not be blinded to the troponin results, during this feasibility pilot, they will not deviate from their normal chest pain triage and destination plans based on the results of troponin testing or HEART score. The routine chest pain triage and destination plans for these EMS counties include obtaining an IV, ECG, and the administration of aspirin, nitroglycerin, and supplemental oxygen. Also, during this pilot, i-STAT troponin and HEART Score results will not be used to determine the destination hospital for transportation. The worksheet completed by the paramedics as part of this pilot will not be included in the patient’s permanent medical record. Paramedics will share i-STAT troponin results with the ED care team as part of their typical transfer of care reports, but will do so using a study specific form, which clearly states that this POC troponin value is for study purposes only and is not to be used to determine a patient’s clinical care. We will train ED nurses and providers that EMS POC troponin results are part of a pilot, should not be acted on clinically at this time, and require confirmation with a core-lab troponin.

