### Exclusion Criteria

1. ST-segment elevation in contiguous leads on any electrocardiogram (>/= 1 mV)
2. Inter-facility transfers
3. Short Pre-hospital times: Scene time + Transportation time anticipated to be less than 5 minutes.
4. Unstable vital signs: symptomatic hypotension at the time of enrollment (systolic < 90 mm Hg), tachycardia (HR>120), bradycardia (HR<40), and hypoxemia (<90% pulse-oximetry on room air or normal home oxygen flow rate)
5. Known terminal diagnosis with life expectancy less than 1 year
6. Concomitant non-cardiac medical, surgical, or psychiatric emergency

b. Sources of Materials

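### The numbered ECG exclusion has no time anchor and a doubtful voltage unit, and it contradicts the STEMI exclusion stated elsewhere in the protocol

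*Protocol*

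**What the plan says.** The protocol states the ECG exclusion in several places and in different terms.

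- **D3 Exclusion Criteria, item 1, and J1 Exclusion Criteria, item 1:** "ST-segment elevation in contiguous leads on any electrocardiogram (>/= 1 mV". There is a voltage threshold, every ECG appears to count, and no time limit is given.
- **A1 Methods and D4 Pilot Design:** "Patients with acute ST elevation myocardial infarction on initial pre-hospital ECG and patients being transferred from another hospital will be excluded". One specific tracing is named, with no voltage threshold.
- **D3 Participation:** the target population has chest pain or similar symptoms "but without obvious ACS on ECG", and STEMI is excluded without a threshold or a named tracing. The same section adds: "Based on STEMI rates at WFBMC we expect less than 5% of patients with acute chest pain to be excluded due to ECG criteria".
- **J1, Human Subjects Involvement and Characteristics:** patients having an acute STEMI are to be excluded, again with no threshold and no named tracing.

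Two other eligibility items also differ. Exclusion 5 is "Patient receiving hospice care" in D3 but "Known terminal diagnosis with life expectancy less than 1 year" in J1. The age limit is "Age greater than or equal to 21" in both inclusion lists, but D3 Participation has "patients >21 years old with acute chest pain", and A1 and D4 also say over 21.

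**The concern.** The primary analysis estimates the sensitivity of the paramedic's HEART classification for 30-day MACE, so eligibility decides who enters the denominator. In an accuracy study, eligibility should rest on what was known when the index test was done.

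The D3/J1 wording does not secure that. E1 says participants are identified retrospectively and that ECG results are abstracted from the hospital record. A1 says an ECG is expected in the ED. Someone applying item 1 from the record can therefore see tracings made after the paramedic's score, and no section bars their use. Take a patient with a non-diagnostic first ECG, a low-risk score and a later ST-elevation infarction. Under E2 this is a missed MACE. The A1/D4 rule keeps the patient; the D3/J1 rule can remove them.

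The voltage is a second, separate problem in the same sentence. Taken literally it sets so high a bar that few STEMIs would be excluded, contrary to the plain STEMI exclusion in A1, D3 Participation, D4 and J1.

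**Working it through.** **Inputs.** From F2: target sensitivity 98%, lower 95% confidence bound above 90%, at least 50 MACE events, MACE rate 10%, total 500. From F3: exact binomial 95% intervals. From D3 Participation: under 5% excluded on ECG. The protocol gives no rate of late or sub-threshold ST elevation, so the counts of missed and affected cases below are assumed for illustration.

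**Plan's own figure.** N = events / MACE rate = 50 / 0.10 = 500. This reproduces.

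**Weight of one case.** 1/50 = 2.0 percentage points of sensitivity.

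**Timing: a MACE case removed because of a later ECG** (exact 95% intervals)

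| Situation | Sensitivity | Interval |
|---|---|---|
| 50 MACE, 2 missed, none removed | 48/50 = 96.0% | 86.29% to 99.51% |
| One missed case removed | 48/49 = 97.96% | 89.15% to 99.95% |
| One detected case removed instead | 47/49 = 95.9% | 86.02% to 99.50% |
| 50 MACE, 3 missed, none removed | 47/50 = 94.0% | 83.45% to 98.75% |
| Two missed cases removed | 47/48 = 97.9% | 88.93% to 99.95% |

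Removing missed cases raises the estimate; removing a detected case lowers it slightly. None of the rows reaches 98%, and none has a lower bound above 90%.

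**Unit: STEMIs left in by a literal 1 mV threshold.** Assumption from outside the protocol: 10 mm per mV, so 1 mV × 10 mm/mV = 10 mm. The ceiling on affected patients is 5% × 500 = 25; the protocol says less than 5%, so 25 is an upper limit and not an expectation. Start from 46/50 = 92.0% and assume that every added STEMI is a MACE scored high-risk:

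- 5 added: 51/55 = 92.7%
- 10 added: 56/60 = 93.3%
- 25 added: 71/75 = 94.7%, with the MACE share rising from 10% to 75/525 = 14.3%

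If a single added STEMI were scored low-risk instead, the result would be 46/51 = 90.2%. The direction depends on how such patients score, and the protocol does not settle that. The ECG item in Table 1 has no ST-elevation row, and the test limitations in K2 warn that troponin may be absent for the first 4 to 6 hours.

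**Source of each effect.** Both come from the D3/J1 sentence. The A1/D4 wording uses the first pre-hospital tracing and no voltage, and produces neither.

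**The case against.** The best defence is that eligibility is a field decision. Paramedics are trained to identify suitable patients (A1, D4). Neighbouring exclusions are judged at the scene: the anticipated pre-hospital time, and hypotension at enrolment. On that reading, item 1 means any tracing up to enrolment, and retrospective identification concerns data collection only. The 1 mV figure would be a slip that four other statements of the STEMI exclusion override in practice.

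Much of this stands. A reader might infer that item 1 definitely reaches ED, inpatient or return-visit tracings. The text does not say so; it only fails to rule them out. Yet item 4 of the same list carries a time anchor for hypotension and item 1 carries none, so the favourable reading has to be supplied by the reader.

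Three further inferences are tempting and are not supported:

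- *The two wordings force a choice between keeping STEMIs and deleting missed events.* Both effects belong to the D3/J1 wording alone.
- *Both effects inflate sensitivity.* That is plausible for evolving STEMIs that scored low-risk, but 47/49 and 46/51 show that the opposite sign is possible. Nothing in the protocol fixes the mix.
- *Dropping one missed case would turn failure into success.* 48/49 is 97.96%, just under 98%, and its exact lower bound of about 89% is below the 90% set in F2.

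**Conclusion.** The eligibility rule is wrong as written because it contradicts itself on which ECG counts and on whether a voltage threshold applies. The contradiction is certain from the text. The consequence is conditional: later tracings can remove MACE cases from the denominator only if staff use them, which the D3/J1 wording allows. The threshold lets STEMIs in only if it is applied literally, and that depends on the usual ECG calibration, which the protocol does not state.

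With about 50 events, each missed case reclassified or removed moves sensitivity by about 2 points. That matters for a 98% target, but the net size and sign of any bias cannot be determined from the protocol. I rate this as moderate, not as a must-fix.

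The mismatch in exclusion 5 is genuine, since the two versions describe different populations, but no size can be put on it. The age wording affects only patients aged exactly 21 and is minor.

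**What to change.** Put one criteria list in the protocol and make A1, D3 (criteria and Participation), D4 and J1 agree with it.

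1. Tie the ECG exclusion to tracings available before the paramedic's HEART score is recorded.
2. State that ST elevation first seen later is not an exclusion but outcome information, to go to adjudication under E4.
3. Reconcile the voltage threshold and its unit with the STEMI definition the investigators intend. No threshold is proposed here.
4. Reconcile exclusion 5 between D3 and J1, and settle the age limit.

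The cost is amendment wording. A few evolving STEMIs will stay in the cohort, so sensitivity may read slightly lower than if they were dropped.

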**Participation**

The target population is adult patients with acute chest pain or other symptoms suggestive of ACS, but without obvious ACS on ECG, who are being transported to WFBMC ED. Therefore, patients >21 years old with acute chest pain, without evidence of an ST-segment elevation myocardial infarction (STEMI) on ECG, will be included. Based on STEMI rates at WFBMC we expect less than 5% of patients with acute chest pain to be excluded due to ECG criteria.

This pilot has been selected for implementation based on collaborations across multiple disciplines including Emergency Medicine, Cardiology, and Prehospital Medicine. As a quality improvement project with broad-based support from local and state EMS systems, participation by human subjects will be part of customary care. Patients treated and transported for acute chest pain by paramedics in Forsyth, Surry, and Stokes County, specifically trained for this investigation, will have data abstracted from their EMS records. In EMS quality assurance projects, it is customary for EMS agencies to contact their patients by phone to assess their well-being. Therefore, each patient will be contacted 30-90 days following their pre-hospital encounter to determine if they have had MACE (cardiac death, acute myocardial infarction, and coronary revascularization), hospitalizations, and objective cardiac testing (stress testing and coronary angiography). Patients will also have index and outcome data abstracted from their WFBH EMR. These data will be reviewed to ensure the feasibility and accuracy of pre-hospital chest pain risk stratification by paramedics using the HEART score and i-STAT POC troponin assay. These quality assurance activities will be performed under a waiver of informed consent, obtained from the Institutional Review Board, as is currently utilized for similar quality surveillance programs at WFBH (i.e. the HEART Pathway Implementation).

### D4. Pilot Design

To ensure the feasibility and accuracy of prehospital chest pain risk stratification, using the HEART score and Abbott i-STAT POC troponin, we propose an **observational implementation design**. Since this pilot is observational it will not need a Clinical Laboratory Improvement Amendments (CLIA) certificate.

*i-STAT validation in moving ambulance:*, A validation of the i-STAT POC troponin assay in a moving ambulance will be performed. Previous study of the Abbott i-STAT POC troponin device showed high correlation between results in a moving ambulance compared with a laboratory environment. However, this is a small study and local validation is required before our paramedics and ED physicians use POC troponin results to influence clinical care. The first step of the i-STAT device validation will be to measure QC samples in a moving ambulance. Next, we will validate whole blood samples from all 500 patients by comparing i-STAT and central lab troponin results. These patients will have testing from the same blood draw with the Abbott i-STAT troponin assay in the ambulance followed by testing with the central lab assay: AccuTnI+3 assay (Beckman Coulter, California) or TnI-Ultra assay (Siemens, Munich Germany). The assay will be considered validated if the agreement between POC and central values (on “elevated” or “normal” results) in QC and patient samples is excellent; as defined by a kappa value >0.74. Validation will be done concurrent with the pilot implementation. The central lab troponin measurement will be run on whole blood obtained at the same time as blood used for the prehospital i-STAT. Please see Appendix 2 for the WFBMC Laboratory purposed method validation and quality control plan.*HEART Score Implementation Pilot:* Prior to implementation, over 70 paramedics will be trained to use the Abbott i-STAT device for POC troponin analyses and to calculate a HEART Score. Educational sessions will train the paramedics to correctly identify subjects appropriate for inclusion in the pilot and to correctly calculate a HEART Score. The educational tools will include in-person teaching and may include self-learning. Similar teaching methods and modules that have been used in the HEART Pathway Implementation (PI [name]) will be used in these sessions. Training regarding use of the Abbott i-STAT device will be conducted by Abbott Laboratories Inc. trainers. This will include the proper storage, maintenance, and use of device cartridges, quality assurance checks, and the interpretation and reporting or results. In addition to initial training, Abbott will provide full training and competency support for 1 year. Training and competency events for all testing personnel will be conducted at start-up, at 6 months, and at 12 months. Documentation of training and competency will be completed. There is no intent to publish this quality control data.

Next, we will begin implementation in ambulances in Forsyth County, Surry County, and Stokes County. Eligible patients for this observational pilot implementation will be adult patients, over 21 years old, with non-traumatic chest pain or symptoms concerning for ACS, being transported to WFBMC ED. Patients with acute ST elevation myocardial infarction on initial pre-hospital ECG and patients being transferred from another hospital will be excluded. In addition, patients will be excluded when paramedics estimate that the patient’s pre-hospital time (scene time + transportation time) will be less than 5 minutes.

Paramedics will use a worksheet to obtain the historical and clinical data needed to calculate a HEART score. This will include performing POC troponin testing. This is within the scope of practice of paramedics who routinely start IVs and perform POC testing on acutely ill patients. Furthermore, the feasibility of performing POC troponin analyses in a moving ambulance has been previously established.[^20-22^](#_ENREF_20) While the paramedics will not be blinded to the troponin results, during this feasibility pilot, they will not deviate from their normal chest pain triage and destination plans based on the results of troponin testing or HEART score. The routine chest pain triage and destination plans for these EMS counties include obtaining an IV, ECG, and the administration of aspirin, nitroglycerin, and supplemental oxygen. Also, during this pilot, i-STAT troponin and HEART Score results will not be used to determine the destination hospital for transportation. The worksheet completed by the paramedics as part of this pilot will not be included in the patient’s permanent medical record. Paramedics will share i-STAT troponin results with the ED care team as part of their typical transfer of care reports, but will do so using a study specific form, which clearly states that this POC troponin value is for study purposes only and is not to be used to determine a patient’s clinical care. We will train ED nurses and providers that EMS POC troponin results are part of a pilot, should not be acted on clinically at this time, and require confirmation with a core-lab troponin.

*Rationale for not blinding paramedics and ED physicians to POC troponin results*: This is a clinical implementation pilot with a goal of testing the feasibility and accuracy of HEART score assessment using POC troponin results. A troponin result is a required component of the HEART score. Therefore in order to calculate a HEART score paramedics cannot be blinded to POC troponin results. Furthermore, through this implementation project we hope to gain greater understanding of the barriers and facilitators of a real-world implementation of the HEART score and POC troponin testing in a prehospital environment. Therefore, our implementation must closely match the expected paramedic workflow. In addition, we believe that asking unblinded paramedics to not share POC troponin results with receiving ED care team is unethical. In some patients POC troponin testing in the prehospital setting may provide early recognition of an acute myocardial infarction (non-ST-segment elevation myocardial infarction) and medics will be ethically compelled to share this information. However, since the POC troponin results are part of a pilot and their accuracy has not yet been confirmed, the paramedics will share results using a study specific form, which clearly states that this POC troponin value is for study purposes only and is not to be used to determine a patient’s clinical care. We will train ED nurses and providers that EMS POC troponin results are part of a pilot, should not be acted on clinically at this time, and require confirmation with a core-lab troponin. It is important to note that patients will already be receiving standard care for a possible NSTEMI. As part of their existing chest pain triage and destination plans paramedics will already be delivering standard care for acute myocardial infarction (aspirin, supplemental oxygen, and nitroglycerin). ED providers also routinely give patients with chest pain and possible NSTEMI aspirin, supplemental oxygen, nitroglycerin, and in high-risk cases use anticoagulation and antiplatelet therapy.

While the ED care team will receive report on the POC troponin results (as well as the patient’s clinical features and ECG, as part of a normal EMS verbal report), the ED care team will remain blinded to paramedics’ HEART Scores to allow evaluation of agreement between paramedic and ED provider risk assessments. HEART Score calculation by the ED provider is part of the standard ED care for patients with acute chest pain presenting to the WFBMC ED, which will facilitate assessment for agreement.

To assess the correlation of pre-hospital POC troponin to in hospital POC troponin and central lab troponin, patients in the WFBMC ED will receive a standard ED chest pain evaluation, expected to include an ECG and serial blood draw at ED arrival and 3 hours after arrival for troponin measurement. Blood obtained in the hospital as part of normal care will be used for central lab troponin measurement [AccuTnI+3 assay (Beckman Coulter, California) or TnI-Ultra assay (Siemens, Munich Germany)]. In addition, whenever possible, this blood will also be used to obtain an in-hospital Abbott i-STAT POC troponin measurement. See Table 2 for a summary of troponin measurements.

| Table 2. Troponin measures | | |  |
| --- | --- | --- | --- |
| **Blood Draw #** | **Description** | **i-STAT**  (green-top tube) | **Central lab/Beckmans**  (green-top tube) |
| 1 | Pre-hospital | X^*^ | X^#^ |
| 2 | ED arrival | X^#^ | X^#^ |
| 3 | 3 hours after ED arrival | X^#^ | X^#^ |

For quality assurance, participants will be identified retrospectively and data will be collected electronically using EHR (EMS records, and WFBH medical records) and via telephone follow-up calls. In EMS quality assurance projects, it is customary for EMS agencies to contact their patients by phone to assess their well-being. Therefore, each patient will be contacted 30-90 days following their pre-hospital encounter to determine if they have had MACE (cardiac death, acute myocardial infarction, and coronary revascularization), hospitalizations, and objective cardiac testing (stress testing and coronary angiography). Patients will also have a record review to determine patient demographics and project outcomes including; MACE, hospitalization, hospital length of stay, and objective cardiac testing.

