## C. Primary Aims

- **Specific Aim 1:** Perform validation (quality control) of the Abbott i-STAT^®^ point-of-care troponin assay in an ambulance; comparing troponin measurements from patient’s blood samples analyzed in a moving ambulance vs a laboratory setting.
- **Specific Aim 2**: Determine whether paramedics using the HEART score and Abbott’s i-STAT^®^ point-of-care troponin assay in the pre-hospital setting can achieve 98% sensitivity and negative predictive value for major adverse cardiac events (MACE: cardiac death, myocardial infarction, or coronary revascularization) during the index visit and at 30 days in patients with symptoms concerning for ACS.
- **Specific Aim 3:** Test whether the inter-rater reliability (kappa) for risk assessment using the HEART score and Abbott’s i-STAT^®^ point-of-care troponin assay between ED physicians and paramedics exceeds 0.60.
- **Specific Aim 4:** Determine the potential impact of prehospital HEART Score and Abbott i-STAT^®^ point-of-care troponin measurement on the following efficiency outcomes: ED length of stay (LOS), hospitalization rate, and rate of objective cardiac testing (stress testing and coronary angiography).
- **Specific Aim 5**: Determine whether pre-hospital Abbott i-STAT^®^ point-of-care troponins are independent predictors of MACE during index hospitalization and at 30 days in patients with symptoms concerning for ACS.

Rationale for the Selection of Outcome Measures

In order for a chest pain risk stratification tool to be considered effective and achieve widespread adoption in the prehospital setting it must accurately detect patients with MACE and there must be high agreement between the paramedics and ED providers. While the HEART Score and troponin testing are well validated for risk stratification in the ED setting, feasibility and accuracy in the prehospital setting have yet to be tested as part of a clinical implementation. Furthermore, the inter-rater reliability (kappa) between paramedics and ED providers has not been tested.

Rationale for 30 day follow-up period

MACE outcomes will be assessed from the index visit through 30 days. ED ACS risk stratification evaluations have traditionally focused on 30 day end-points as recommended in the standardized reporting guidelines for ACS.[^19^](#_ENREF_19)

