**Validation (Accuracy)**

- - - - 20 QC samples (level 1, 2, and 3) tested in a moving ambulance
- **Will occur concurrently with pilot implementation**

We will compare test samples between i-STAT and the Core Lab troponin method.

i-STAT tested from a FULL lithium heparin green top tube, collected in the field and tested immediately after collection. Blood will NOT be transferred from one collection container to another collection container. The SAME green top tube to be sent to the Core Lab for testing upon arrival to WFBH Emergency Department.

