*Hematocrits in the range of 0-65% PCV have been demonstrated not to affect results. Samples with hematocrit levels above this range have demonstrated increases in the test imprecision and quality check codes.*

*The analyzer must remain on a level surface with the display facing up during testing. Motion of the analyzer during testing can increase the frequency of suppressed results or quality check codes. A level surface includes running the handheld in the downloader/recharger.*

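### Aim 1 promises patient troponin results from a moving ambulance, but the patient-sample procedure does not require motion and the kappa rule does not separate moving from stationary runs

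*Protocol*

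**What the plan says.** Specific Aim 1 (section C, and the same aim in the Abstract) compares patients' "blood samples analyzed in a moving ambulance vs a laboratory setting". Section D4 carries the same claim: "A validation of the i-STAT POC troponin assay in a moving ambulance will be performed".

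The validation has two legs.

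- **QC leg.** D4: "The first step of the i-STAT device validation will be to measure QC samples in a moving ambulance". Attachment K2, under Validation (Accuracy): "20 QC samples (level 1, 2, and 3) tested in a moving ambulance".
- **Patient leg.** D4: "we will validate whole blood samples from all 500 patients by comparing i-STAT and central lab troponin results", and then "These patients will have testing from the same blood draw with the Abbott i-STAT troponin assay in the ambulance". K2 describes the tube as "collected in the field and tested immediately after collection". Neither place repeats the motion condition.

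D4 accepts the assay as validated if agreement on elevated versus normal gives kappa above 0.74 in QC and patient samples. No split by vehicle motion is given there or in section F3. The worksheet list in E1 includes date and time elements but no item for motion. K2, under Test Limitations, warns: "Motion of the analyzer during testing can increase the frequency of suppressed results or quality check codes".

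**The concern.** Motion is the condition that the aim names, and the protocol's own device information treats it as a factor in performance. Yet a patient sample drawn and tested before the ambulance leaves the scene complies fully with the written procedure, and its result counts towards the same kappa as a sample run on the road. If many runs are of that kind, the patient-sample result says little about motion but would still be described as validation in a moving ambulance.

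The failure that K2 links to motion is also of a kind that the criterion cannot see. A suppressed result or a quality check code gives no troponin value, so there is no elevated/normal pair and the run drops out of the kappa.

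This matters because D4 says that local validation is needed before paramedics and ED physicians let these results influence care, and the project is meant to support a larger implementation. Readers of that later work would take the moving-ambulance statement at face value.

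**Working it through.** The protocol gives no computed figure for Aim 1 (F2 sizes the study for MACE sensitivity only), so there is nothing to reproduce. The check sets the texts side by side and then asks how much the pass rule could hide.

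**Step 1. Where motion is required**

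| Element | Place | Motion |
|---|---|---|
| Aim 1, patients' blood | Abstract; C | moving |
| D4 statement of the validation | D4 | moving |
| QC samples | D4; K2 | moving |
| Patient test | D4 | in the ambulance, motion not stated |
| Patient test | K2 | immediately after a field draw, motion not stated |
| Pass rule, kappa > 0.74 | D4 | not distinguished |
| Worksheet data | E1 | times listed, motion not listed |

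The exclusion criteria (D3) define pre-hospital time as scene time plus transportation time. Part of the window in which a test can be run is therefore stationary. They do not say when blood is drawn.

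**Step 2. Share of samples that the procedure ties to motion**

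Share = QC samples / (QC samples + 500 patients).

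- 20 QC samples in total: 20/520 = 3.8%.
- 20 at each of three levels (K2 can be read either way): 60/560 = 10.7%.

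In both cases all of it is control material and none is patient blood.

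**Step 3. What a pooled patient kappa can conceal**

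Assumptions, none of them protocol figures: 10% of results are elevated by each method, the same in moving and stationary runs; stationary kappa (k_s) is 0.85, 0.90 or 0.95; the moving share (m) is 10% to 75%.

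With equal marginals, chance agreement is the same in both strata: 0.1² + 0.9² = 0.82. Kappa is then linear in observed agreement, so the pooled value is the weighted mean:

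k_pooled = (1 − m) × k_s + m × k_m

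Setting k_pooled = 0.74 and solving for the moving-run kappa:

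k_m = (0.74 − (1 − m) × k_s) / m

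Example with k_s = 0.90 and m = 0.50: (0.74 − 0.45)/0.50 = 0.58.

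| k_s | m = 75% | m = 50% | m = 25% | m = 10% |
|---|---|---|---|---|
| 0.85 | 0.70 | 0.63 | 0.41 | −0.25 |
| 0.90 | 0.69 | 0.58 | 0.26 | −0.70 |
| 0.95 | 0.67 | 0.53 | 0.11 | −1.15 |

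Any moving-run kappa above the tabulated value lets the patient leg pass. With these marginals kappa cannot fall below −0.1/0.9 = −0.11, so at 10% moving no result in the moving runs could make the pooled value fail. At 75% moving, the rule already fails once the moving-run kappa drops to about 0.67 to 0.70, so little is hidden.

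**Step 4. Suppressed results**

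Kappa uses only runs with both an i-STAT and a central laboratory result. Whatever fraction of moving runs is suppressed, the kappa of the remaining pairs does not register the loss. A separate rate is needed to show it.

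**The case against.** Several stronger readings are tempting, and the protocol does not support them.

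- *The whole validation could pass on parked runs.* It could not. The criterion also covers QC samples, and those are run in motion. The weakness is confined to the patient-sample leg.
- *Patient samples are tested out in the field, away from the vehicle.* In K2 the field is where the tube is collected. D4 places the test in the ambulance.
- *Most patient runs will be stationary.* Nothing says so. Scene time appears only in the definition of the short-interval exclusion, and immediate testing is equally compatible with a draw during transport.
- *Motion makes elevated samples read as normal.* K2 speaks of suppressed results and quality check codes, not of wrong values. D4 also cites an earlier study with high correlation between moving-ambulance and laboratory results, although it calls that study small and asks for local validation. The low moving-run kappas above are break-even values, not forecasts.

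Three further arguments deserve weight. Aim 1 itself states the condition for patients' blood, so the procedure may simply fail to repeat it. That is possible, but compliance is judged against the procedure, and nothing planned would show whether the condition was met. Next, a split by motion may be left to a statistical analysis plan, which is not at hand. Here, however, the protocol itself fixes the aim, the procedure and the pass rule, and these do not match. Last, D4 wants the pilot to follow the expected paramedic workflow, so agreement over all runs estimates performance as used. That stands: the overall kappa is a legitimate quantity and should stay. It supports a claim about in-ambulance testing, not about motion.

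**Conclusion.** The point holds for the patient-sample part of Aim 1. Its aim specifies motion, its procedure does not require motion, and its criterion cannot tell whether motion was tested. The text comparison alone establishes this.

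The practical size depends on the share of runs made while moving, which is unknown. Under the assumptions of the working, the consequence is slight if about three quarters of runs are moving, and it is substantial at a quarter or fewer. The documents do not show that the device performs poorly in motion, or that the planned verdict would be wrong. They show that the patient data, analysed as described, could not settle the matter. The correction is cheap and worth making.

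**What to change.** 1. Classify each patient run as stationary or moving, by comparing the i-STAT run time with the EMS depart-scene and arrival times. E1 lists date and time elements and EMS records are a data source, but it does not say that these particular times are captured. If they are not, add one box to the worksheet. State in advance how a run that straddles departure or arrival is classified.
2. Keep the overall kappa and its 0.74 threshold. Beside it, report kappa with its 95% confidence interval separately for moving and stationary runs. Moving runs need not become the sole basis of the pass rule.
3. Report the rate of suppressed results and quality check codes in each stratum, with all attempted runs as the denominator.
4. Claim validation in a moving ambulance for patient samples only if the moving runs support it. Otherwise restate Aim 1 and D4 as testing in the ambulance.

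The cost is one derived variable or one worksheet box; field procedure does not change. The moving subset will have a wider interval. At the same prevalence and kappa, width grows roughly as 1/√m: about 1.4 times the full-sample width if half the runs are moving (1/√0.50 = 1.41), and 2 times if a quarter are (1/√0.25 = 2.0).
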